### Supplemental EBRT

From 4 to 8 weeks after ^125^I-BT, 45 Gy of EBRT in 25 fractions is routinely delivered by three-dimensional conformal radiation therapy (3D-CRT) using ≥ 6 MV photons or intensity-modulated radiation therapy (IMRT). Generally, a daily fraction of 1.8 Gy will be administered 5 days per week for 5 weeks. If the D90 form the implant is < 100 Gy up to the total dose of 50.4 Gy (1.8 Gy × 28) and if the dose is > 140 Gy the EBRT will be reduced to 39.6 Gy (1.8 Gy × 22).

3D-CRT will be delivered with 4 or more fields isocentric beam setup based on CT. The technical aspects of IMRT delivery are institution-dependent.

The clinical target volume (CTV) is defined as the prostate and the proximal seminal vesicle (SV) within 1 cm from the prostate-SV junction [19]. No attempt is made to treat the pelvic lymph nodes. A planning target volume (PTV) is applied to the CTV such that there is a block margin of 1.5-2 cm around the CTV. Position verification and correction are performed by standard port film imaging in the case of 3D-CRT and with orthogonal film isocenter verification in the case of IMRT.

### Contents of HTx

HT with CAB consists of a subcutaneous LH-RHa administration in conjunction with oral antiandrogen for 3 months before and continuing for 3 months after ^125^I-BT. After 6 months of HT, the patients were assigned to receive no further HT treatment or to continue HT with the same LH-RHa but without the antiandrogen for an additional 2 years. Bicalutamide (80 mg/day) is used as an oral antiandrogen, and either goserelin acetate (3.6 mg per month or 10.8 mg every 3 months) or leuprolide acetate (3.75 mg per month or 11.25 mg every 3 months) is subcutaneously injected as LH-RHa.

### Data collection

This study design was chosen to ensure accurate, standardized, and high-quality data collection. All patients giving written informed consent to the study are asked to complete a short family history and epidemiology questionnaire. Electronic Data Capture (EDC) systems are used to collect clinical data in electronic format, with clinical data being obtained from patient medical records by the Translational Research Informatics Center. A follow-up data form is completed by the Clinical Trials Practitioner (CTP) at diagnosis, 3, 6, 9, 12, 15, 18, 21, 24, 27, and 30 months, and then every 6 months until 84 months from the date of commencement of CAB. These forms capture information regarding patient characteristics, disease presentation, diagnosis and treatment, PSA, recurrence and survival. Annual follow-up is continued until death, loss to follow-up, or the end of the active phase of the study (September 2022).

### Definition of endpoints

The primary endpoint is biochemical progression-free survival (bPFS). Biochemical progression is defined as an increase in PSA of ≥ 2 ng/mL from the nadir value following treatment. Secondary endpoints are: 1) OS, 2) clinical progression-free survival (local progression, distant failure), 3) disease-specific survival (DSS), 4) salvage therapy non-adaptive interval, 5) QOL, and 6) adverse events. OS and PFS are calculated from the 1st day of treatment to death from any cause and or to identification of disease progression or death, respectively. Local progression is defined as local tumor reappearance at the primary site. Local tumor reappearance will be confirmed by rectal examination and imaging studies, such as magnetic resonance imaging (MRI) or CT or biopsy when indicated. The primary endpoint and the secondary endpoints are the bPFS at 7 years and OS (or DSS) at 10 years, respectively, following initial HT with CAB to investigate the relationship between results and eventual recurrence after completion of trimodality therapy.

### Planned statistical analyses

It has been shown that the 7-year bPFS rate ranges from 67.8% to 83% in patients with high-risk PCa who undergo combination of BT and EBRT or trimodality treatment [5,20]. Based on these two reports, the 7-year bPFS rate of the short-term HT group is estimated to be 75%. On the other hand, the 7-year bPFS rate of the long-term HT group is estimated to be 87.5% (*i.e*., hazard ratio = 0.464) based on three RCTs comparing EBRT plus long-term HT with EBRT alone [10-12]. Taken together, 153 patients for each group are needed to detect a significant difference between treatments by log-rank test with a significance level of 0.05 and a power of 80%. Given the further assumption that approximately 10% of randomized patients will not be evaluable for various reasons, the target sample size was set at 170 patients per group (340 total).

Statistical analyses will be performed on an intention-to-treat basis. Survival curves will be estimated using the Kaplan-Meier method. The log-rank test will be used to test for differences in survival curves between the two groups of patients. The hazard ratio will be estimated using the Cox proportional hazard model. The longitudinal change of QOL scores (IPSS, SF-8™, EPIC) between diagnosis and 60 months following ^125^I-BT will also be compared between groups. Patients will be evaluated for toxicity, graded according to the National Cancer Institute Common Toxicity Criteria version 4.0 (http://evs.nci.nih.gov/ftp1/CTCAE/About.html). For all patients, the incident proportion of grade 3 adverse events will be compared between groups by Fisher's exact test. All tests will be two-sided, and a *P*-value of 0.05 will be considered statistically significant. Five years after the last patient is recruited, an interim analysis will be performed and the results will be reported to the Independent Data Monitoring Committee.

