Some previous studies demonstrated a benefit of HT used in conjunction with EBRT to treat locally advanced prostate cancer [10-12]. However, these studies, which demonstrated an advantage with the addition of HT, were done when the radiation dose may have been inadequate to control all local disease. The question therefore that has never been answered is what benefit, if any will long-term androgen deprivation have when much higher radiation doses are delivered. Although the ABS recommends HT in conjunction with BT for cytoreduction of prostate volume, there are no clear indications for using adjuvant HT in intermediate- to high-risk PCa [7]. Moreover, both neoadjuvant and adjuvant HT may significantly induce adverse events, including fatigue, diminished sexual function, and hot flushes and possible early death [13,14]. Accordingly, investigation of the best optimal duration of HT with maximization of outcome while minimizing toxicity is a logical step in the management of localized high-risk PCa, because the prolonged use of HT may result in an increase in adverse events. It is necessary to determine which patients with high-risk PCa will actually benefit from HT despite some compromises in quality of life (QOL) associated with the adverse event profile of this treatment.

As mentioned above, the optimal RT-based trimodality protocol for use in high-risk PCa remains controversial. However, there have been no prospective studies regarding the efficacy and safety of trimodality treatment with combined HT, EBRT, and BT for high-risk patients. Such prospective clinical trials are necessary. Here, we describe our study protocol for high-risk PCa, which is a phase III, multicenter, randomized controlled trial (RCT) of a trimodality treatment protocol with BT using iodine-125 (^125^I-BT), EBRT, and neo-adjuvant and concurrent HT for 6 months with or without adjuvant HT for 2 years. We also assessed whether short-term HT without adjuvant HT or long-term HT with adjuvant HT is better with regard to improved local control and biochemical cure rate in high-risk localized PCa. The final goal of this study is to establish an appropriate treatment strategy for high-risk PCa without increasing the occurrence of adverse events.

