### Eligibility criteria - Inclusion criteria

Patients must:

a. Be from 40 to 79 years of age when obtaining written informed consent.

b. Have high-risk PCa with a definitive histological diagnosis by needle biopsy. In this study, high risk is defined as those cases in which where at least one of the following three conditions is satisfied: 1) PSA > 20 ng/mL prior to CAB, or 2) clinical stage of T2c or T3a, or 3) Gleason score ≥ 8 as determined by central pathological judgment.

c. Performance status of 0-1, according to the Eastern Cooperative Oncology Group.

d. Previously untreated for PCa.

e. Appropriate bone marrow, hepatic, and renal function as demonstrated in laboratory tests within two weeks prior to registration.

a) WBC ≥ 3000/μL.

b) Hemoglobin level ≥ 10.0 g/dL.

c) Platelet count ≥ 10.0 × 10^4^/μL.

d) Serum creatine level ≤ 2.0 mg/dL.

e) ALT and AST levels ≤ 100 IU/L.

f. Computed tomography (CT) and bone scan without evidence of metastases

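### Kaplan-Meier is the only curve estimator named, so 10-year disease-specific survival will somewhat overstate the absolute risk of prostate-cancer death; cumulative incidence should be reported beside it

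*Protocol article*

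**What the plan says.** The section Planned statistical analyses of the protocol article gives the time-to-event methods in three general sentences. The first is "Survival curves will be estimated using the Kaplan-Meier method". The second assigns the comparison of arms to a log-rank test, and the third takes the effect measure from a Cox model. None names an endpoint, makes an exception or mentions competing events.

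The section Definition of endpoints lists among the secondary endpoints "3) disease-specific survival (DSS), 4) salvage therapy non-adaptive interval". It sets the horizon at 7 years for biochemical progression-free survival (bPFS) and at 10 years for OS or DSS. It states that "OS and PFS are calculated from the 1st day of treatment to death from any cause" for OS, and that PFS ends at progression or death. It gives no event or censoring rule for DSS or for the salvage interval.

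Two other places bear on the point. The inclusion criterion on age reads "Be from 40 to 79 years of age when obtaining written informed consent". The Background ends a list of harms of HT with "and hot flushes and possible early death".

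**The concern.** Kaplan-Meier suits OS, and it suits PFS endpoints that count death as an event. DSS is different: a man who dies of something else can no longer die of prostate cancer. If his death counted as an event, the endpoint would be OS, so under Kaplan-Meier he can only be censored. The estimator then treats him as still at risk of the cancer death that he can no longer have. The resulting curve describes a population in which no one dies of anything else, and one minus that curve is higher than the proportion of men who actually die of prostate cancer.

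This matters more with a long horizon and older men. A man who enters at 79 is 89 at the 10-year reading. It also matters that the randomized contrast is HT duration and that the protocol itself raises early death as a possible harm of HT, so the competing risk could differ between arms. The absolute 10-year risk of prostate-cancer death by arm is the figure that readers would weigh against the burden of two more years of treatment.

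**Working it through.** **Inputs from the protocol article.** Kaplan-Meier, log-rank and Cox as the stated methods; DSS at 10 years; age 40 to 79; 7-year bPFS of 75% and 87.5%; hazard ratio 0.464; 153 per group raised to 170. **Assumed, because the article gives no figures.** Prostate-cancer death, salvage and other-cause death rates at 10 years; constant, independent cause-specific hazards.

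**Step 1: the plan's own figures.**
- ln(0.875)/ln(0.75) = 0.4642, against 0.464 stated.
- A two-proportion calculation (two-sided 0.05, 80% power) gives 152 per group, against 153 stated.
- 153/0.9 = 170, as stated.

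These figures concern bPFS. By the stated PFS definition, death is an event, so the competing-risk question does not touch them.

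**Step 2: what Kaplan-Meier shows for DSS.** Let C be the true 10-year cumulative incidence of prostate-cancer death and O that of other-cause death. With constant hazards, the total cumulative hazard is H = -ln(1 - C - O), the cancer part is H × C/(C + O), and one minus Kaplan-Meier is 1 - exp(-cancer part).

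Example, C = 10% and O = 20%: H = -ln(0.70) = 0.3567; cancer part = 0.3567/3 = 0.1189; one minus Kaplan-Meier = 1 - exp(-0.1189) = 11.2%.

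| True cancer-death risk | Other-cause death 10% | 20% | 30% |
|---|---|---|---|
| 5.0% | 5.3% | 5.6% | 6.0% |
| 10.0% | 10.6% | 11.2% | 12.0% |

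The ratio of shown to true risk is 1.05 to 1.06, 1.12, and 1.19 to 1.20 across the columns.

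**Step 3: the same check from the other direction.** Fix one minus Kaplan-Meier at 5%, 10% or 15%, and let other-cause mortality on its own be 10% to 30%. With cumulative hazards Lc and Lo at 10 years, cumulative incidence = Lc/(Lc + Lo) × (1 - exp(-(Lc + Lo))). Kaplan-Meier then overstates by 0.25 points (5% shown, 4.75% actual) to 2.3 points (15% shown, 12.7% actual).

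**Step 4: the salvage interval, if deaths before salvage are censored.** The same formula, with one minus Kaplan-Meier of 15% to 35%, gives an overstatement of 0.7 to 5.2 points.

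**Step 5: an excess of other-cause deaths in one arm.** Assume the same cancer hazard in both arms (Kaplan-Meier DSS 90%) and other-cause mortality, taken on its own, of 20% against 30%.

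| 10-year quantity | Arm with 20% | Arm with 30% |
|---|---|---|
| Kaplan-Meier DSS | 90% | 90% |
| OS | 0.90 × 0.80 = 72% | 0.90 × 0.70 = 63% |
| Cumulative incidence, cancer death | 9.0% | 8.4% |
| Cumulative incidence, other-cause death | 28% - 9.0% = 19.0% | 37% - 8.4% = 28.6% |

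The DSS curves are identical. OS shows the excess. The cancer-death incidence taken alone makes the arm with more deaths look slightly better, so it must be shown with other-cause death.

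**The case against.** The sentence on Kaplan-Meier names no endpoint, and the article defines no censoring rule for DSS or the salvage interval. It condenses a full protocol, and an analysis plan that is not shown could add competing-risk methods. For the salvage interval this objection stands: if death counts as an event there, as it does for PFS, Kaplan-Meier is correct. For DSS it stands only in part. The unseen plan may add cumulative incidence, but the stated method covers a survival endpoint on its ordinary reading, and DSS leaves no option but to censor other-cause deaths.

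The effect is also modest and rests on assumed rates. With 170 men per arm, simple binomial 95% margins are about ±3.3 points around 5% (1.96 × √(0.05 × 0.95/170)) and ±4.5 points around 10%. An overstatement of 0.6 or 1.2 points at 20% other-cause death lies well inside them. That stands, although the overstatement is systematic and does not shrink with more patients. One can also say that Kaplan-Meier DSS estimates a legitimate net quantity. It does, but that quantity is not the risk patients face.

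A reader might infer that the plan hides non-cancer deaths caused by long-term HT. The documents do not support this: OS from any cause is a planned secondary endpoint at 10 years, death counts in PFS, and adverse events are compared. Only the DSS curve, and possibly the salvage curve, is blind to such deaths.

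**Conclusion.** The point holds as a minor one. With Kaplan-Meier as the only named estimator, the 10-year DSS figures will overstate the absolute risk of prostate-cancer death by about 5% to 20% in relative terms. This rests on constant, independent hazards and an assumed 10% to 30% other-cause mortality at 10 years. The article gives no rates and no age distribution, so the true size could lie outside this range. For the salvage interval the conclusion is conditional on a censoring rule that the article does not state.

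It would be wrong to conclude that the comparisons are invalid. Censoring other-cause deaths leaves the log-rank test and the Cox model valid for the cause-specific hazard. What is affected is the description of absolute risk, and how far the DSS curve can be interpreted without OS beside it.

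**What to change.** Add to the analysis plan:

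- For DSS, report the Aalen-Johansen cumulative incidence of prostate-cancer death with other-cause death as the competing event. Show the cumulative incidence of other-cause death by arm next to it, and read both together with OS.
- For the salvage interval, state whether death is part of the endpoint. If it is not, report cumulative incidence with death before salvage as the competing event.
- Keep the cause-specific log-rank and Cox analyses for the comparison of arms, and keep Kaplan-Meier for OS, bPFS and clinical PFS.

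The cost is a few sentences and a little extra analysis and reporting. Cause of death is already needed for DSS, so that part requires no new data, and the sample size and the primary analysis do not change.

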**Methods/Design:**

This is a phase III, multicenter, randomized controlled trial (RCT) of trimodality with BT, EBRT, and HT for high-risk PCa (TRIP) that will investigate the impact of adjuvant HT following BT using iodine-125 (^125^I-BT) and supplemental EBRT with neoadjuvant and concurrent HT. Prior to the end of September 2012, a total of 340 patients with high-risk PCa will be enrolled and randomized to one of two treatment arms. These patients will be recruited from more than 41 institutions, all of which have broad experience with ^125^I-BT. Pathological slides will be centrally reviewed to confirm patient eligibility. The patients will commonly undergo 6-month HT with combined androgen blockade (CAB) before and during ^125^I-BT and supplemental EBRT. Those randomly assigned to the long-term HT group will subsequently undergo 2 years of adjuvant HT with luteinizing hormone-releasing hormone agonist. All participants will be assessed at baseline and every 3 months for the first 30 months, then every 6 months until 84 months from the beginning of CAB.

The primary endpoint is biochemical progression-free survival. Secondary endpoints are overall survival, clinical progression-free survival, disease-specific survival, salvage therapy non-adaptive interval, and adverse events.

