### Methods of recruitment and random allocation

Recruitment of patients is supported by the tri-modality therapy with ^125^I-BT and EBRT and short- or long-term HT for High-risk Localized PCa (TRIP) Study Group. Recruiting began in October 2010, and is planned for completion by September 2012. All prostatic biopsy histological slides of newly diagnosed prostate cancer since the initiation of the study have been reviewed by central pathologists, with patient eligibility determined at the time of review. Eligible patients are randomly assigned to one of two treatment arms through the data center at the TRI. Randomization is done centrally using a minimization method to obtain good between-group balance for factors including age category (< 70/≥ 70), PSA category (≤ 20/> 20 ng/mL), Gleason score by central pathological judgment category (< 8/≥ 8), and institutions.

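### Allocation is minimized on age, PSA, Gleason score and institution, but the primary log-rank test and Cox model name no strata or covariates, which makes the analysis mildly conservative if those factors are prognostic

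*Protocol article*

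**What the plan says.** In the protocol article, Methods of recruitment and random allocation: "Randomization is done centrally using a minimization method to obtain good between-group balance for factors including age category" (<70/≥70). The other factors are PSA (≤20/>20 ng/mL), central Gleason score (<8/≥8) and institution. On institutions, the abstract says: "These patients will be recruited from more than 41 institutions".

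Planned statistical analyses gives the primary test: "The log-rank test will be used to test for differences in survival curves between the two groups of patients". It gives the estimate: "The hazard ratio will be estimated using the Cox proportional hazard model". Neither sentence names a stratum or a covariate. The same section sizes the trial on that comparison, "by log-rank test with a significance level of 0.05 and a power of 80"%, from marginal 7-year rates: "the 7-year bPFS rate of the short-term HT group is estimated to be 75"% and "the 7-year bPFS rate of the long-term HT group is estimated to be 87.5"%, stated as "hazard ratio = 0.464". The article does not say that the analysis will be unadjusted. It is silent.

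**The concern.** Minimization removes chance imbalance between the arms on the balanced factors. If those factors predict outcome, the treatment estimate varies less from trial to trial than under simple randomization. A plain log-rank test does not know this: its variance still allows for imbalance that the allocation has prevented, so it rejects too seldom.

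The article supports the premise that some of the factors matter. PSA >20 and Gleason ≥8 are two of its three high-risk criteria, and the Discussion links Gleason score, PSA and stage to adverse pathology, and that pathology to biochemical failure. It gives no effect sizes, and says nothing on the prognostic role of age or institution.

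At stake is a modest amount of power in a trial expecting only about 57 primary events, using factors already recorded for every randomized man. A prespecified choice also prevents picking between a plain and a stratified test once results are seen.

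**Working it through.** **1. Reproduce the sample size.** Inputs from Planned statistical analyses: 75% against 87.5%, two-sided 0.05, 80% power, 10% not evaluable.

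- Hazard ratio: ln(0.875)/ln(0.75) = 0.464, as stated.
- Two proportions: 152 per group.
- Freedman: events = (1.960 + 0.842)² × [(1 + 0.464)/(1 − 0.464)]² = 58.6. The mean event rate is (0.25 + 0.125)/2 = 0.1875, so 58.6/0.1875/2 = 156 per group.
- Stated: 153 per group, close to both. 153/0.90 = 170 per group, 340 in total.
- Expected events in 306 men: 306 × 0.1875 = 57.4.

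The sizing therefore reproduces, and it is for a plain, unstratified comparison of marginal rates.

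**2. Simulate the plain and stratified analyses.** From the article: 306 men, the four minimization factors, 41 institutions as the lower bound, 7-year follow-up, and marginal rates held at 75% against 87.5% (75% in both arms under the null). Assumed, because the article gives no figures: biased-coin probability 0.8; prevalence 50% age ≥70, 40% PSA >20, 50% Gleason ≥8; the prognostic hazard ratios and institution SD (log-hazard scale) shown below. There were 10,000 runs per scenario. The Monte Carlo standard error is √(0.05 × 0.95/10,000) = 0.2 points for an error rate near 5% and √(0.8 × 0.2/10,000) = 0.4 points for power near 80%.

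Under the null:

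| Prognostic HR (age/PSA/Gleason), institution SD | Model SE ÷ true SD, plain Cox | Error rate, plain log-rank | Error rate, stratified on three factors (8 cells) |
|---|---|---|---|
| 1/1/1, 0 | 1.000 | 4.96% | 4.84% |
| 1/1.5/1.5, 0 | 1.010 | 4.55% | 4.67% |
| 1.2/2/2, 0 | 1.038 | 4.18% | 4.65% |
| 1.2/2/2, 0.4 | 1.052 | 3.74% | 4.18% |
| 1.5/3/3, 0.5 | 1.093 | 3.15% | 4.28% |

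Power:

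| Scenario | Plain log-rank | Stratified on three | Cox with three factors | Stratified on institution | All four crossed |
|---|---|---|---|---|---|
| 1/1/1, 0 | 80.8% | 80.1% | 80.4% | 77.1% | 38.3% |
| 1/1.5/1.5, 0 | 80.8% | 80.6% | 80.9% | 77.9% | 38.1% |
| 1.2/2/2, 0 | 81.5% | 82.1% | 82.5% | 78.1% | 38.2% |
| 1.2/2/2, 0.4 | 81.6% | 82.2% | 82.5% | 79.2% | 39.5% |
| 1.5/3/3, 0.5 | 82.4% | 84.9% | 85.2% | 80.2% | 40.6% |

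The move from the plain log-rank to the three-factor analyses ranges from −0.7 points (no prognostic effect) to +2.5 (stratified test) or +2.8 (Cox) in the strongest scenario. A separate simulation on the same marginal rates gave type I error of about 3.4–4.4% for the plain test and 4.5–5.1% for the stratified test, with a gain of about 0 to 3.5 points.

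**3. Where the gain comes from.** In the 1.2/2/2 scenario without an institution effect, the mean log hazard ratio is −0.779 with SE 0.2845 unadjusted, and −0.803 with SE 0.2849 adjusted. The ratios are 0.779/0.2845 = 2.74 and 0.803/0.2849 = 2.82. The interval does not narrow. The estimate moves from about exp(−0.779) = 0.459 (marginal) to exp(−0.803) = 0.448 (conditional).

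**4. Why institution is different.** With 41 sites, 57.4/41 = 1.4 events per site. Crossing 41 sites with the 8 cells gives 328 strata for 306 men, so most strata carry no comparison between arms.

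**The case against.** The strongest objection is that the article is condensed, never calls the analysis unadjusted, and may leave strata and covariates to the full protocol or SAP. That stands as a limit: if those documents name the strata, nothing needs changing. It does not remove the point, because the article does name its primary test and sizes the trial on it, and a better choice is available from data already collected.

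Several stronger readings are tempting, and the documents do not support them.

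- *False positives.* A reader might infer that the mismatch inflates type I error. It does the opposite.
- *The 80% power is lost.* Sub-80% figures appear if 0.464 is applied as a conditional hazard ratio within prognostic cells: with Gleason and PSA hazard ratios of 4 and 2.5, plain power is 78.4%, but long-term-arm bPFS is then only 86.9%. The article derives 0.464 from marginal rates. Holding 75% against 87.5% gives 83.0% in that same setting, and at least 80.8% in every scenario tabulated.
- *Adjustment narrows the interval, or the plain hazard ratio is biased.* The model standard error is too large relative to true sampling variation, but the adjusted interval is no narrower. The unadjusted hazard ratio is a different, marginal quantity, and is the one that matches the design effect.
- *The analysis must follow every minimization factor.* For institution this costs power, severely so when all four factors are crossed.

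It also stands that the size of the gain depends on assumed inputs, and that a plain log-rank test is valid and defensible.

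**Conclusion.** The point holds as a minor matter of efficiency and prespecification, not of validity. If the plain analyses are run as named and the balanced factors are prognostic, the primary test works at about 3% to 4.6% instead of 5% and gives up about 0 to 3.5 points of power. If the factors are not prognostic there is no loss, and stratifying would itself cost under 1 point (80.8% to 80.1%). The direction follows from the design. The size rests on assumed prevalences, prognostic strengths, institution variation and biased-coin probability, none of which the article gives.

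**What to change.** State that the primary test is a log-rank stratified by age (<70/≥70), PSA (≤20/>20 ng/mL) and central Gleason score (<8/≥8). Estimate the primary hazard ratio from a Cox model with the same three factors, labelled as conditional, and report the unadjusted hazard ratio as supportive. State that institution is not a stratum and enters only a sensitivity analysis. Adding T stage is optional and not part of this change. Fix the choice before any outcome comparison by arm is seen, including the planned interim analysis.

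The cost is one sentence of text and no new data. The trade-offs are a conditional instead of a marginal primary hazard ratio, and under 1 point of power if the factors turn out not to be prognostic. If the SAP already specifies this, no change is needed.

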### Additional measures

Two validated QOL questionnaires, the SF-8™, which has been translated into Japanese, and the Expanded Prostate Cancer Index Composite (EPIC), will be administered prior to hormonal therapy and at the 60 months after the beginning of CAB to comprehensively cover the various aspects of physical and psychosocial wellbeing.

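### The quality-of-life comparison is stated as change from baseline with no mention of baseline adjustment; if left unadjusted it is valid but less precise than it need be

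*Protocol article*

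**What the plan says.** The *Planned statistical analyses* section of the protocol article defines the QOL comparison by its outcome: "The longitudinal change of QOL scores (IPSS, SF-8™, EPIC) between diagnosis and 60 months" following I-125 brachytherapy "will also be compared between groups". It names no test, model or covariate for QOL. The same section does name methods for other outcomes: Kaplan-Meier, log-rank and Cox for survival, and Fisher's exact test for grade 3 adverse events. All tests are two-sided at 0.05.

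*Additional measures* describes the collection. SF-8 and EPIC "will be administered prior to hormonal therapy and at the 60 months after the beginning of CAB", which is one baseline and one follow-up assessment. IPSS is not named there.

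*Definition of endpoints* places QOL fifth of six secondary endpoints: "4) salvage therapy non-adaptive interval, 5) QOL, and 6) adverse events". The trial is sized on biochemical progression-free survival (bPFS) only: "153 patients for each group are needed to detect a significant difference between treatments by log-rank test with a significance level of 0.05". No standard deviation, effect size, correlation or power is given for any QOL score.

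*Methods of recruitment and random allocation* minimizes on age, PSA, Gleason score and institution. Baseline QOL is not among the factors.

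**The concern.** With one baseline score and one late score, a simple difference carries the noise of both. Over a gap of about five years the two scores may be only moderately correlated, and then subtracting the baseline can add more noise than it removes. Using the baseline as a covariate removes only the part of it that predicts the later score.

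The article's *Background* presents the benefit of hormone therapy as something to be weighed against its cost in quality of life. The trial is not sized for QOL, and SF-8 and EPIC have a single follow-up assessment, so the power to show a lasting cost of long-term therapy depends largely on how efficiently those two scores are used. An unadjusted change would give a wider confidence interval than the same data allow.

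**Working it through.** **The plan's own figure.** The article gives no figure for QOL, only for bPFS, and that figure reproduces.

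- Hazard ratio = ln(0.875)/ln(0.75) = 0.464, as stated.
- Freedman's formula at two-sided 0.05 and 80% power gives 59 events. The mean event probability is (0.25 + 0.125)/2 = 0.1875, so 59/0.1875/2 ≈ 157 per group (156 without rounding the events). A comparison of two proportions gives 152. The stated 153 lies in this range.
- 153/0.90 = 170 per group, as stated.

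The 153 is used below only as an illustrative number of men per arm with both QOL scores.

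**Inputs for QOL.** Two time points (*Additional measures*) and two-sided 0.05 (*Planned statistical analyses*). Assumed, because the article gives none: equal variance σ² at both times, and a correlation ρ varied over a range.

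**Formulas.**

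- Unadjusted change: variance = 2(1 − ρ)σ².
- 60-month score adjusted for baseline: variance = (1 − ρ²)σ².
- Ratio, adjusted to change = (1 + ρ)/2, so the reduction is (1 − ρ)/2.
- Smallest difference detectable with 80% power, in SD units = (1.96 + 0.84) × √(2V/153), with V the relative variance.
- Power at a difference of 0.3 SD = Φ(0.3/√(2V/153) − 1.96). The 0.3 SD is an illustration, not a figure from the article.

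| ρ (assumed) | V, change | V, adjusted | Variance cut | Detectable difference, change vs adjusted (SD) | Power at 0.3 SD, change vs adjusted |
|---|---|---|---|---|---|
| 0.3 | 1.40 | 0.91 | 35% | 0.379 vs 0.306 | 60% vs 79% |
| 0.5 | 1.00 | 0.75 | 25% | 0.320 vs 0.277 | 75% vs 86% |
| 0.7 | 0.60 | 0.51 | 15% | 0.248 vs 0.229 | 92% vs 96% |
| 0.8 | 0.40 | 0.36 | 10% | not computed | not computed |

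Ignoring the baseline altogether has V = 1, so below ρ = 0.5 the unadjusted change is noisier than the 60-month score alone.

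**Checks.** A simulation with 153 per arm and ρ = 0.5 gave a variance ratio of 0.77 against the theoretical 0.75. In the same simulation, regressing the change on arm and baseline gave exactly the same arm effect as regressing the 60-month score on arm and baseline.

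**If the variances differ.** With σ₀ at baseline and σ₁ at 60 months, the variance of change minus the adjusted variance is σ₀² + σ₁² − 2ρσ₀σ₁ − (1 − ρ²)σ₁² = (σ₀ − ρσ₁)². This is never negative. The size of the gain depends on the equal-variance assumption; its direction does not.

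**The two QOL sections side by side.** *Additional measures* counts the 60 months from the start of combined androgen blockade (CAB) and names SF-8 and EPIC. *Planned statistical analyses* counts them from I-125 brachytherapy and adds IPSS. *Contents of HTx* places brachytherapy 3 months into CAB, so the second origin falls at about 60 + 3 = 63 months from the start of CAB. In *Data collection*, forms after month 30 come every 6 months from the start of CAB, so months 60 and 66 are scheduled and month 63 is not.

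**The case against.** The strongest objection is that the article does not specify an unadjusted test. It names an outcome, the change, and leaves the model open. Change analysed with baseline as a covariate is the same test as the analysis proposed here, so the present sentence is compatible with the fix. An article may also leave the covariates of a secondary model to an analysis plan that is not shown. This stands, and it makes the loss conditional. It does not dispose of the point: the sentence names change as the quantity compared and mentions no adjustment, and its natural reading is an unadjusted comparison.

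Two stronger readings are tempting, and the document supports neither.

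- A reader might infer that the trial loses a quarter of its QOL precision. The 25% needs ρ = 0.5 and equal variances, and the article gives neither. The power figures also rest on an illustrative 0.3 SD difference and on 153 men per arm, which is the bPFS requirement and not a count of completed 60-month questionnaires.
- A reader might infer bias through regression to the mean. Under randomization an unadjusted change comparison is unbiased and keeps its type I error. Baseline QOL is not a minimization factor, so a chance baseline difference can move the result in a given trial, but that is part of the same loss of precision and not a separate fault.

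**Conclusion.** The point holds as a conditional matter of efficiency. If the change is compared without baseline adjustment, the comparison is valid, but its variance is higher than necessary. Adjustment would cut that variance by (1 − ρ)/2, which is 35% at ρ = 0.3, 25% at 0.5 and 10% at 0.8, assuming equal variances at the two times. The correlation is assumed throughout and may differ between scores. If the analysis plan already adjusts change for baseline, nothing is lost and only the wording needs to say so.

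Separately, and without any assumption, the two QOL sections disagree on the origin of the 60 months and on the list of instruments. For SF-8 and EPIC a baseline is documented; for IPSS the article does not show that it is collected on the same schedule.

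The consequence is confined to the precision of a secondary endpoint. The bPFS analysis and the sample size are untouched.

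**What to change.** Replace the QOL sentence in *Planned statistical analyses* with one to this effect: each 60-month QOL score will be compared between groups by analysis of covariance, with the baseline score and the non-institution minimization factors (age, PSA and Gleason categories) as covariates, and the adjusted mean difference will be reported with its 95% confidence interval. Keep the mean change per arm as a descriptive summary.

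In the same edit, make *Additional measures* and *Planned statistical analyses* agree on whether the 60 months run from the start of CAB or from I-125 brachytherapy, and state whether IPSS is collected on that schedule.

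The analysis change costs one sentence and needs no new data or visits for SF-8 and EPIC. The reconciliation is a wording change, provided it matches what sites are already collecting.
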